### Dietary assessment

Dietary assessment is performed by means of two 24-hour dietary recalls, dietary habits and qualitative food frequency questionnaires (FFQ) which completed during face-to-face personal interviews by expert dietitians, with at least 5 year of experience in the nationwide food consumption survey project [33]. The first interview is conducted at the subject's home and the second at the clinic of TLGS within 1–3 days after the first visit. The interviewers use photographs of household portions in order to confirm exact food intakes as household measures. Food values are usually recorded as household measures. Mothers are asked about the type and quantity of meals and snacks when children are unable to recall. The 24-hour dietary recall describes reported intakes from midnight to midnight, meal after meal. The questionnaire is validated in the nationwide household food consumption survey project which has been reported in Persian [34]. The recall method is useful for estimating intakes in culturally diverse populations such as Tehran, representing a wide range of foods and eating habits. Standard reference tables are used to convert household portions to grams [35]. Data are entered into the nutritionist III package and Mosby Nutritrac Softwares to obtain daily energy, nutrient intakes and servings of foods consumed. For mixed dishes, food groups and nutrients are calculated according to their ingredients. These two days are among usual days for subjects, excluding holidays. The dietary habit questionnaire is completed during the first interview in order to obtain the usual dietary habits. It includes questions about sprinkling salt on food, the consumption of fried, fast and high fat foods, fruits and vegetables, nuts, sweets, and the kinds of meats and dairy products. In addition dietary data related to past year are collected using 168 item FFQ adopted from Willett format [36]. Subjects are asked to estimate their consumption of different food items on a daily, weekly or monthly basis. Validation study showed that correlation coefficients for energy-adjusted intakes between two FFQs ranges from 0.40 to 0.87 and correlation coefficients between FFQ and 24-hour dietary recalls range from 0.32 to 0.72, and are not substantially different between genders [37].

### Biochemical measurements

All laboratory kits are supplied by Pars Azmon Inc., Iran. Serum total cholesterol and triglycerides are measured using enzymatic calorimetric tests with cholesterol esterase and cholesterol oxidase and glycerol phosphate oxidase, respectively. HDL-C is measured after precipitation of the apolipoprotein B containing lipoproteins with phosphotungistic acid. LDL-C was calculated from the serum TC, TGs, and HDL-C concentrations expressed in mg/dl using Friedwald formula [38] if TGs concentration is lower than 400 mg/dl. Assay performance was monitored in every 20 tests interval using the lipid control serum, Precinorm [normal range] and Precipath [pathologic range] wherever applicable (Boehringer Mannheim, Germany; cat. no. 1446070 for Precinorm and 171778 for Precipath). Lipid standard (C.f.a.s, Boehringer Mannheim, Germany; cat. no. 759350) is used to calibrate the Selectra 2 auto-analyzer (Vital Scientific, Spankeren, Netherlands) on all days of laboratory analyses. Serum glucose concentration is assayed using enzymatic colorimetric method with glucose oxidase technique. Assay performance is monitored at every 20 test intervals using the glucose control serum, Precinorm [normal range] and Precipath (pathologic range) wherever applicable (Boehringer Mannheim, Germany; cat. no. 1446070 for Precinorm and 171778 for Precipath). Glucose standard (C.f.a.s, Roche, Germany; cat. no. 759350) is used to calibrate the Selectra 2 auto-analyzer on all days of laboratory analyses. All samples are analyzed when internal quality control met the acceptable criteria. Inter- and intra-assay coefficients of variations are both 2.2% for serum glucose and 2 and 0.5% for TC and 1.6 and 0.6% for TGs, respectively.

### DNA extraction

Buffy coats are separated from EDTA-anti coagulated samples. Genomic DNA is extracted from the Buffy coats with salting out method [39]. The concentration and purity of the extracted DNA are assayed by nanodrop. The DNA samples are stored in aliquot at 4°C and back-up DNA samples are stored at -20°C. More than 20 μg genomic DNA with a 260/280 ratio of 1.8–2.1 is available from each family member.

### Outcome measurements

Every participant of the TLGS is followed up for any medical event during prior year by telephone call. He/she is asked for any medical conditions by a trained nurse and if a related event had occurred a trained physician collects complementary data during a home visit. If necessary, she pays a visit to respected hospital and collects data from medical files. In the case of mortality, data are collected from hospital or death certificate by local physician.

Collected data, are evaluated by an outcome committee consisted of principal investigator, internist, endocrinologist, cardiologist, epidemiologist and physician who collected outcome data; other experts are invited for evaluation of NCD disorders as needed. Specific outcome for every event is assigned according to ICD-10 criteria and AHA classification for cardiovascular events [40,41].

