#### Secondary

Secondary research goals include determining differences in the prevalence of major NCD risk factors and outcomes between intervention and control groups with special focus on angina pectoris, myocardial infarction, cerebrovascular events, diabetes mellitus, hypertension and dyslipidemia.

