**Figure 1 F1:**
[figure not shown]
**The minimum and maximum distances between intervention and control groups are 1.5 and 5 kilometers, respectively**. Map of areas of control (C) and intervention (I) groups.

A total of 5630 subjects under coverage of one of the three health centers which is far from two other centers (Figure 1), were considered for lifestyle modification using primary, secondary and tertiary preventions for NCD.

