Twelve schools, 7 guidance and 5 high schools, across the intervention area and 15 schools (7 guidance and 8 high schools) across the control area are enrolled in the program. The living tobacco-free intervention program in schools consisted of four components: classroom curriculum and practice, students activities in school anti-tobacco society, anti-tobacco policies in school and family (parents) involvement. The intervention approach combines constructs from social learning theory and principles of Iranian culture and practices. At beginning of first year of program implementation in schools, all the principals and volunteer teachers are trained by physicians and dietitian in 2-day teaching seminars in order to enable team to educate schoolchildren in matters related to lifestyle modification. Related teaching programs in schools contain 4 main and 3 review lessons. Topics in these lessons are prevalence of smoking and its short term and long term consequences, psychology of coping with stress and methods of quieting smoking. Nutrition educational program includes three 30-minute nutrition classes per semester. The staff members who deliver the interventions are different from those who collect the data. The parental component of the intervention include two 45-minute nutrition classes in academic year and one class per year for teachers whom educate schoolchildren with the aim of promotion of food habits. The content of the nutrition lessons parallels the information offered in children's curriculum with the objective of introducing food groups based on food guide pyramid and nutrition concepts such as trying low-fat foods and dairies, high fiber diets, and healthy snacks. Food bulletin and pamphlets covers dietary issues for parents. The baseline survey showed that high fat, high sugar and salty snacks were sold in schools. After explaining to school officials, and schoolchildren, red labels are used for unhealthy snacks and green labels for healthy foods. Participation of parents are suggested by cooking healthy traditional foods and sold with low price to children. In each phase, KAP study of dietary issues is performed to help for further educational program.

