### Biostatistical considerations

#### Sample size

For baseline data collection, based on predicted prevalence rates of 30% for dyslipidemia in people <30 and 45% for those ≥ 30 years of age, confidence interval of 95%, study power of 80%, attrition rate of 20%, design effect of 2% for seven age groups and two sexes, sample size was calculated to be 14280. Therefore, 15005 subjects were selected randomly from areas covered by 3 health centers. In phase 2 of TLGS, based on 5% decrease in serum cholesterol, two gender, three age groups, 5% design effect and 30% attrition rate, sample size for intervention group was calculated as 4750 subjects. Therefore, population covered by one of the 3 health centers (5630 people) selected for intervention and 9375 subjects under coverage of other two centers used as controls.

Because of the wide scope of the project and variety of the measured variables, different types of analyses are performed, depending on the type of the reports or the variables and outcomes.

Although the original of this study was based on reducing hypercholesterolemia, however, in all subjects including those less healthy or normals, changes in other risk factors, NCD, and outcomes delineated in this study will also be followed in statistical considerations.

In most of analyses we will considered each individual separately, however, for interfamilial relations we will consider intraclass correlations in analyses. It should be also mentioned that in multistage cluster random sampling procedure, each health center in district 13 was a cluster and families in three randomly selected centers were recruited. Continuous data are expressed as their measures of location and spread in total and subgroups. For qualitative and categorized continuous variables, percentages and frequency distributions are reported.

Normality of distribution of the continuous variables will be examined using histograms, measures of skewness and kurtosis, Kolmogrove-Smirnove test and sometimes Chi-square test. When log-transformed values are used, geometric means are computed. Percentiles will be used to describe the high or low values of the skewed variables. When assumptions of the parametric statistical methods are not met, nonparametric methods of their counterparts will be used. These methods also were used for analysis of variables, not originally continuous, such as attitudes, quality of life etc.

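### The committee that classifies events includes the physician who collected the data at the participant's home, so at least one classifying member knows the arm

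*Protocol article*

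**What the plan says.** Three parts of the protocol article bear on this point.

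- **Who classifies.** Outcome measurements gives the composition: "Collected data, are evaluated by an outcome committee consisted of principal investigator, internist, endocrinologist, cardiologist, epidemiologist and physician who collected outcome data". Other experts may be invited, and outcomes are assigned by ICD-10 and, for cardiovascular events, the AHA classification.
- **How the collecting physician gets the data.** A nurse telephones each participant yearly, and "if a related event had occurred a trained physician collects complementary data during a home visit", with a hospital visit if needed. For deaths the route differs: "In the case of mortality, data are collected from hospital or death certificate by local physician".
- **How arm is set.** The Sample size section says: "Therefore, population covered by one of the 3 health centers (5630 people) selected for intervention and 9375 subjects under coverage of other two centers" served as controls. The caption of Figure 1 adds: "The minimum and maximum distances between intervention and control groups are 1.5 and 5 kilometers, respectively".

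The Secondary research goals compare the groups "with special focus on angina pectoris, myocardial infarction, cerebrovascular events, diabetes mellitus, hypertension and dyslipidemia". The section on the steering committee makes the principal investigator a member, alongside the program coordinators. The one stated separation of roles stands under Schools: "The staff members who deliver the interventions are different from those who collect the data".

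**The concern.** Participants in a community lifestyle program cannot be blinded, and here arm is a matter of address. Those who decide whether a reported event counts, and as what, can be kept unaware of address. The stated composition does not do this. It seats at the table a person who has seen the address, next to the principal investigator, who helps to oversee the program under test.

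At stake are the events whose label depends on judgement: myocardial infarction, cerebrovascular events, angina reported as a clinical event, and cause of death. If borderline cases are read even slightly differently in the two areas, the comparison of incidence carries a bias that a larger sample does not shrink. A large study makes such a bias more likely to reach nominal significance.

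**Working it through.** **Step 1. Does any classifying member know the arm?**

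- Residence determines health centre, and health centre determines arm (Sample size: one centre with 5630 people against two with 9375; 5630 + 9375 = 15005).
- The areas are 1.5 to 5 km apart (Figure 1), so a home address identifies the arm.
- The collecting physician visits the home and is listed among those who evaluate the data (Outcome measurements).

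For non-fatal events, at least one member therefore knows the arm. For deaths the link is looser. The data come through a local physician, and the article does not say whether that is the physician who sits on the committee.

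**Step 2. Do the stated safeguards hide the area?**

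- ICD-10 and AHA criteria narrow the judgement but do not conceal area.
- Separate delivery and data-collection staff is stated under Schools. It keeps the collector from being the person who delivered the program there, but not from knowing the area.
- The only mention of masking is under Retention. It concerns results and is listed as an obstacle to keeping participants.

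Neither safeguard hides the area.

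**Step 3. Which outcomes pass through the committee?**

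| Outcome | Basis in the article | Depends on the committee? |
|---|---|---|
| Hypertension, dyslipidaemia, diabetes by glucose test | Numeric cut-offs (Definitions for risk factors), three-yearly examination | No |
| Rose angina | Questionnaire read by published guidelines | No |
| ECG-defined CHD | Minnesota codes by two independent physicians, 10% recoded by a third | No |
| All-cause death | Fact of death | No |
| Myocardial infarction, cerebrovascular event, clinically reported angina, cause of death | Assigned by the committee | Yes |

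**Step 4. What could it amount to?** The plan has no figure to reproduce and gives no event or confirmation rates. All inputs here except the group sizes are assumptions.

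If a fraction c_I of true events is confirmed in the intervention area and c_C in control, then

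observed RR = true RR × c_I / c_C.

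With true RR = 1:

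- 0.85 / 0.90 = 0.944, and reversed 0.90 / 0.85 = 1.059
- 0.80 / 0.90 = 0.889, and reversed 0.90 / 0.80 = 1.125

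The chance that such a bias alone gives a nominally significant result in its own direction (two-sided 5%, n = 9375 and 5630, no clustering) is

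Φ[(|p0 − p1| − 1.96 × SE0) / SE1],

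where p0 is the recorded control risk, p1 = p0 × ratio, SE0 is the pooled and SE1 the unpooled standard error.

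Example with p0 = 5% and ratio 0.889: p1 = 0.04444, difference 0.005556, SE0 = 0.003601, SE1 = 0.003551. Then (0.005556 − 0.007058) / 0.003551 = −0.423, and Φ = 0.34.

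| Recorded control risk (assumed) | 0.889 | 0.944 | 1.059 | 1.125 |
|---|---|---|---|---|
| 3% | 21% | 8% | 9% | 25% |
| 5% | 34% | 11% | 12% | 38% |
| 10% | 61% | 20% | 21% | 68% |

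Without bias the chance in one direction is 2.5%. Clustering is ignored, so these figures indicate sensitivity only.

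**The case against.** The strongest case on the other side is that the article lists members and does not describe voting, the contents of the file, or whether address and centre are shown. The collecting physician may only present facts. A committee charter belongs in a full protocol, which is not shown. Several specialties are represented and published criteria apply, so no one classifies alone.

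Part of this stands. Silence on the charter is not an error, and a reader who inferred that masking is impossible for every member would go too far: direct knowledge of area follows for one member, while for the others it is likely but not stated. The objection does not remove the point, because the composition is stated, not omitted, and it names the collecting physician among those who evaluate the data.

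Three further readings are tempting and unsupported:

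- **That the principal investigator leads the intervention.** The article shows steering-committee membership and oversight, no more.
- **That all clinical outcomes are exposed.** Step 3 shows that much of what the study measures, including the serum cholesterol behind the phase 2 sample size, does not depend on the committee.
- **That the bias favours the intervention.** Nutrition and quit-smoking clinics in the intervention program could raise detection there and push the result the other way.

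It is also fair to say that masked classification cannot recover events that unmasked participants never report by telephone.

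**Conclusion.** The point holds in limited form. As composed, the committee has at least one member who knows the arm for events investigated by home visit, and nothing stated masks the rest. This leaves myocardial infarction, cerebrovascular events, clinically reported angina and, less directly, cause of death open to differential classification. The published criteria limit that risk without removing it.

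No size can be taken from the documents. Confirmation ratios between areas of 0.89 to 1.125 would give a spurious relative risk of the same size, and the true ratio could be 1. The conclusion rests on two readings of the text: that residence identifies arm, which is explicit, and that a listed member takes part in classification, which is the plain sense of the sentence but is not spelled out. Nothing here shows that bias has occurred.

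**What to change.** Amend Outcome measurements so that:

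1. the committee classifies from files with address, health centre and program-contact notes removed;
2. the collecting physician supplies facts or answers written queries, but takes no part in classification;
3. the principal investigator also abstains from classification.

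The remaining specialists already on the committee can do the work. The cost is redaction of each file. This is not trivial with 15005 participants and at least 20 years of follow-up, but it arises only for reported events. Because phase II began in January 2002, the report should say from which date masked classification applied.

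The change does not cure unmasked ascertainment by telephone and home visit. All-cause mortality should therefore be read next to the adjudicated events. This adds little work, since the Biostatistical considerations already plan a life-table analysis of mortality.

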### Lifestyle interventions

Interventions are aimed at lifestyle modification through primary, secondary and tertiary preventions for NCD by improving nutrition and dietary pattern, increasing physical activity levels, and smoking cessation. Training sessions for coping with the stress for families, and life skills training for schoolchildren are also performed. A total of 5630 people from district No. 13 were chosen for interventions. The rationale for choosing this area was that the population residing in district No. 13 is stable, medical and health facilities in this district are under the administration of Shahid Beheshti University of Medical Sciences and the intervention area is far away from control areas.

Demographic characteristics of both intervention and control groups are shown in Table 3. Mean age was 34.0 ± 19.2 and 33.0 ± 18.8 years and mean BMI was 24.4 ± 5.9 and 24.2 ± 5.9 kg/m^2 ^and the prevalence of literacy was 92.3 and 92.6% in intervention and control groups, respectively. It is noteworthy that all participants speak Persian and there is no language barrier. There are only 7.5% illiterate people. All others could read and understand materials which are provided for education. The illiterate individuals are older than 50 and are educated face-to-face by staff and other family members.

**Table 3 T3:** Baseline characteristics of the intervention and control subjects

Age Group (years)	Characteristics	Control	Intervention	P Value
3–9	Male(%)	48.9	49.2	0.90
	Literate (%)*	80.1	79.0	0.69
	Mean age (Year)	6.4	6.4	0.54
	Daily Cigarette smoker (%)	0	0	-----
	Mean body mass index (kg/m2)	15.42	15.7	0.13
				
10–19	Male(%)	46.3	48.8	0.16
	Literate (%)	99.8	99.8	0.65
	Employed (%)	1.8	2.1	0.62
	Marital status (Married %)	1.5	2.1	0.25
	Mean age (Year)	14.5	14.6	0.27
	Daily Cigarette smoker (%)	1.5	2.4	0.12
	Mean body mass index (kg/m2)	20.2	20.1	0.45
				
20–29	Male(%)	38.9	35.5	0.10
	Literate (%)	99.7	99.8	0.83
	Employed (%)	30.8	32.5	0.40
	Marital status (Married %)	48.4	51.3	0.12
	Mean age (Year)	24.3	24.4	0.29
	Daily Cigarette smoker (%)	6.7	7.5	0.06
	Mean body mass index (kg/m2)	24.2	24.3	0.87
				
30–39	Male(%)	43.1	41.8	0.50
	Literate (%)	99.5	98.7	< 0.05
	Employed (%)	50.3	50.0	0.86
	Marital status (Married %)	90	86.0	< 0.05
	Mean age (Year)	34.4	34.4	0.44
	Daily Cigarette smoker (%)	15.5	15.1	0.40
	Mean body mass index (kg/m2)	26.5	26.8	0.16
				
40–49	Male(%)	40.5	42.8	0.32
	Literate (%)	96.3	96.1	0.79
	Employed (%)	45.2	46.0	0.74
	Marital status (Married %)	93.7	92.8	0.78
	Mean age (Year)	44.3	44.3	0.70
	Daily Cigarette smoker (%)	17.5	15.3	0.18
	Mean body mass index (kg/m2)	28.1	27.9	0.29
				
50–59	Male(%)	41.3	37.6	.014
	Literate (%)	84.8	84.1	0.73
	Employed (%)	37.1	26.9	< 0.05
	Marital status (Married %)	91.9	90.3	0.51
	Mean age (Year)	54.2	54.3	0.24
	Daily Cigarette smoker (%)	12.3	9.2	0.17
	Mean body mass index (kg/m2)	28.3	28.6	0.17
				
60–69	Male(%)	49.3	49.2	0.96
	Literate (%)	65.8	66.2	0.87
	Employed (%)	18.1	19.0	0.68
	Marital status (Married %)	82.9	81.9	0.59
	Mean age (Year)	64.0	64.2	0.18
	Daily Cigarette smoker (%)	9.5	8.2	0.26
	Mean body mass index (kg/m2)	27.4	27.8	0.13
				
≥ 70	Male(%)	55.9	62.7	0.14
	Literate (%)	44.1	59.5	< 0.001
	Employed (%)	7.7	8.6	0.72
	Marital status (Married %)	70.6	76.2	0.58
	Mean age (Year)	74.1	74.1	0.86
	Daily Cigarette smoker (%)	7.6	9.8	0.83
	Mean body mass index (kg/m2)	26.5	25.9	0.18

* In children >6 years old.

### Dietary interventions

Based on Knowledge, Attitude and Practice (KAP) study results which was conducted with a representative sample of 826 adults and 7669 adolescents, dietary intervention and nutrition education protocols are designed. The KAP study includes questions related to factors of weight change, fat sources, fibers, snacks, food varieties including dairies, grains, fruits, vegetables, nuts, meat, sweets, pats, etc. The KAP study provided clues on requirements and points to implement intervention on healthy nutritional practice and what needs to be changed. The intervention is implemented in following sites.

### Public sites

In 2002, nutrition education classes were held in four days of week and in average 12 adults took part in each session where they were instructed using face to face consultation, showing films and slides together with nutrition recommendations; applicable guidelines for improving healthy dietary patterns were employed to instruct them. In addition, healthy nutrition messages are written in a health newsletter called "paik-e tandorosti" that are distributed every season. Pamphlets introducing food groups, kinds of fats, number of required portions for each age group, guidelines to reduce fat content of foods and prepare healthy recepies have been distributed. In religious meetings lectures about NCD, their complications and prevention by modifying lifestyle strategies and acquiring healthy nutrition pattern are delivered. To increase cost-effectiveness of our study and simplicity, the volunteers are trained and they relate healthy nutritional concepts to members of participated families. Nutrition concepts have also been included. Nutrition interventions in all participants are described under public sites, clinics and under families. Nutrition concepts such as preparing low-fat foods and dairies, high fiber diets, less frying, eating more fruits and vegetables, avoidance of fast foods, unhealthy snacks and tobacco use, in conjunction with adequate physical activity are transformed in all education activities.

